#### Concealment mechanism {16b}

The system will not release the allocation code to the treating surgeon until the patient has been recruited into the trial (on the day of scheduled surgery) to maintain allocation concealment.

#### Implementation {16c}

The senior data engineer will be responsible for generating the allocation sequence and assigning interventions.

### Assignment of interventions: blinding

#### Who will be blinded {17a}

Blinding is not feasible for the treating surgeon or the senior data engineer responsible for coding the randomisation sequence, who will have access to the allocation code and allocation code key. The senior data engineer will not have further involvement in the study beyond the allocation and data coding.

Trial participants will be blinded to the intervention assignment and will be counselled at the time of recruitment regarding both surgical techniques, supplementing the information provided on the participant information sheet and consent form (PISCF). Surgical assistants, practice staff, clinical outcome assessors members of the research team and study statisticians involved in the data analysis will be blinded to the allocation, with access to only the allocation code which will comprise a label where grouping is not able to be inferred.

Postoperative clinical evaluations and assessment of serious adverse events will be conducted by a surgical fellow that is hosted within the clinic on a rotating basis for 6 months. In cases where the surgical fellow assisting with surgery also performs the postoperative evaluation, masking will occur through access to only the allocation coding described above. While the treatment evaluator will have access to postoperative radiographs of the operated structures within the foot, it is expected the intervention allocation cannot be derived from these images. Patients returning for evaluation at the 12-month follow-up will be assessed by a fellow not involved in the surgery.

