### Assignment of interventions: allocation

#### Sequence generation {16a}

Participants will be randomly assigned to receive either a flat-cut Weil osteotomy (control, group A) or wedge-cut osteotomy (experimental, group B) procedure using a central computer-based simple randomisation system, with a 1:1 allocation without blocking. The random allocation sequence will be embedded within the clinical registry via a randomisation algorithm (Matlab 2018b, Mathworks Inc., USA). The allocation will be communicated electronically to the treating surgeon via an allocation code comprising nondescript terminology, whereby the allocation cannot be inferred from the label to other study personnel.

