#### Procedure for unblinding if needed {17b}

In situations where an adverse event or complication has occurred such that reoperation or other invasive intervention is deemed necessary, it may be necessary to unmask the intervention allocation to plan appropriate treatment. Requests to unmask will be made electronically via the treating surgeon and logged within the study masterlist. Requests will be managed by the senior engineer with access to the allocation key.

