## Statistical methods

### Statistical methods for primary and secondary outcomes {20a}

#### Principles

An analyst blinded to treatment allocation will perform the primary and secondary analyses, by comparing the intervention group to the control group. Data will be analysed following intention-to-treat principles (i.e. participants will be analysed in the group to which they were randomised to). Data normality of baseline characteristics and process measures will be evaluated by visual inspection of histograms. Continuous variables will be presented as means and standard deviations for normally distributed variables: median, minimum, maximum and interquartile range for non-normally distributed variables. Frequencies and percentages will be used to summarise categorical variables. Percentages will be calculated using the number of participants for whom data are available as the denominator. Alpha will be set at 0.05 and effect sizes as described in the sample size calculation will be considered of interest.

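### The allocation code is relied on for masking but is open to assistants and outcome assessors; if it is one label per arm, a fellow who assists at one operation can read it for other patients

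*Protocol article*

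**What the plan says.** Sequence generation {16a} has the registry send the treating surgeon an "allocation code comprising nondescript terminology, whereby the allocation cannot be inferred from the label to other study personnel". Who will be blinded {17a} then takes surgical assistants, practice staff, outcome assessors, the research team and the statisticians together and says that they "will be blinded to the allocation, with access to only the allocation code which will comprise a label where grouping is not able to be" deduced.

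The same section has postoperative evaluations done by a surgical fellow on a six-month rotation. It foresees that this fellow may also have assisted at the operation, and names the coding as the masking in that case. For the last visit it adds: "Patients returning for evaluation at the 12-month follow-up will be assessed by a fellow not involved in the surgery".

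Under Principles in the statistical methods, "An analyst blinded to treatment allocation will perform the primary and secondary analyses, by comparing the intervention group to the control group". Intervention description {11a} shows that the arms differ in plain view: group B has a second cut and a piece of bone taken out, and group A does not.

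**The concern.** A code hides the arm only until someone has matched it to a technique. An assistant watches the technique and, under {17a}, has access to the code. If all patients in an arm carry the same label, that one match tells the assistant what the label means for everyone else. Masking would then fail for patients whose operation the fellow never saw.

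At stake is the secondary outcome. Floating toe is rated by hand, and Objectives {7} also counts stiffness, for which the article describes no photographic record. A rater who knows the arm can shift such ratings, and the trial hypothesis is that one arm has fewer complications.

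**Working it through.** The plan states no figure on this point, so there is none to reproduce. The check is a reading of the text followed by a timing calculation.

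**1. Is the code per arm or per patient?** The article does not say. It says that statisticians have only the allocation code ({17a}) and that the blinded analyst compares intervention with control (Principles). Allocation is made "using a central computer-based simple randomisation system, with a 1:1 allocation without blocking", so there are two groups to tell apart. A code unique to each patient does not sort patients into two sets. With the access described, the comparison can be run only if the code is one label per arm. This is an inference from two passages, not stated text.

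**2. What does one observed operation reveal?**
- One label per arm, two arms: one pairing of label and technique identifies both labels. In principle the label of any of the 80 patients can then be read.
- One code per patient: the pairing identifies 1 of 80.

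**3. Does the 12-month rule close the gap?** It bars a fellow involved in the surgery of the patient being assessed. It does not bar one who assisted at other trial operations. With six-month rotations, the fellow on duty 12 months later will normally be a different person anyway, so the rule adds little to what the rotation already ensures.

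**4. How many 12-month visits could be affected?** Assumptions: uniform accrual, visit exactly 12 months after surgery, one fellow per six-month rotation, rotation phase unknown.
- Let R be the recruitment length in months. Operations run over months 0 to R, and visits over months 12 to R + 12.
- Let r, between 0 and 6, be the months left in the rotation that is under way when operations end.
- Share of visits falling to a fellow whose rotation overlapped trial operations = (R − 12 + r) / R.
- R = 24 (Trial status: 12 April 2021 to 12 April 2023): from 12/24 = 50% to 18/24 = 75%, or about 40 to 60 of 80 patients.
- R = 12 (Recruitment {15}): from 0/12 = 0% to 6/12 = 50%, or about 0 to 40 of 80.
- Patients operated on per full rotation: 80 × 6/24 = 20, or 80 × 6/12 = 40. One is enough for the match.

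The patient counts are before any dropout. Overlap is opportunity only: the fellow must also have assisted at a trial operation and noted the label.

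**5. Are earlier evaluations exposed?** Yes, under either recruitment length. Secondary outcome analysis counts complications up to 12 months, and the Cox model in {20b} uses time to detection from day 1. Before 12 months the assisting fellow may be the evaluator. That fellow knows the arm of the patients they assisted on directly, whatever form the code takes.

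**The case against.** The strongest reply is that nothing in the article states a shared label. The wording fits a patient-unique code, the senior data engineer holds the key and is responsible for data coding, and that engineer could already be giving the analyst a separate group label. A journal article may leave the code format to the full protocol.

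Part of this stands: the shared label is inferred, and the point about other patients is conditional on it. But the article is not silent on access. It gives one code to assistants, assessors and statisticians in one sentence and names it as their mask. Either the code is per arm and can be decoded, or the access described does not let the analyst compare arms. Both readings need correcting. The failure to mask a fellow who watched the operation does not depend on the code's form.

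A second reply is that floating toe is recorded on a photograph and defined by contact with the floor, and that the article does not say the clinic fellow is the rater. This lowers the risk for that item if the photographs are rated by someone without the code, which is not stated.

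A third is that other routes to the arm exist: the operation report identifies the technique, and surgical details sit in the practice management system. That is true, and the fix below does not close them.

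**Conclusion.** The point holds in conditional form. The allocation code cannot mask a fellow who assisted at the operation. If it is one label per arm, as the analyst's task implies, it also carries the allocation from one patient to another, and the 12-month rule does not prevent that. The opportunity covers about 50–75% of 12-month visits with 24-month recruitment, or 0–50% with 12-month recruitment, plus earlier evaluations. The two recruitment lengths in the article conflict and should be reconciled.

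The consequence is possible detection bias in the complication outcome. The documents give no basis for estimating its size. The primary outcome is FAOS pain reported by patients, and nothing gives them the code, so it is largely unaffected.

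Three stronger readings are tempting and not supported:
- **One unmasking would decode the whole trial.** Procedure for unblinding {17b} says "it may be necessary to unmask the intervention allocation to plan appropriate treatment", but the request comes through the treating surgeon, who already has the key, and is handled by the engineer. No disclosure to blinded staff is described.
- **Every 12-month assessment is compromised.** Exposure depends on rotation overlap and can be as low as 0%.
- **Statisticians are unblinded by the same route.** They do not watch operations.

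**What to change.** In Sequence generation {16a} and Who will be blinded {17a}:
- Do not give the allocation code to assistants, practice staff or outcome assessors; they work from the patient ID only.
- Release the allocation to the surgeon under a code unique to the patient.
- Have the senior data engineer add a separate two-level arm label to the analyst's dataset only.
- Stop describing the code as masking a fellow who assisted at the operation.

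The cost is a change to the registry's release step and form permissions, revised protocol wording, and one small data merge before analysis. No extra visits are needed. One limit remains: the assisting fellow still knows the arm of the patients they operated on, and the protocol should say so.

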The osteotomy will be stabilised with a Kirschner wire placed across the osteotomy (along the metatarsal shaft) to guide screw fixation. Once the screw is fully engaged, the K-wire will be removed. The overhanging bone ledge will be resected with a bone saw or rasp, followed by releasing of the soft tissues under retraction closure of the joint capsule. The remaining soft tissues will be closed in layers and dressed with strips and bandages. The patient will be moved to recovery and discharged as per normal.

The preparation of the patient and surgery site for group B will be as described for group A (the control intervention). The surgical procedure will be modified by adding a second osteotomy proximally to remove a rectangular wedge of bone for the purposes of shortening the metatarsal and repositioning the floating segment of the metatarsal head proximally to the metatarsal neck [11].

Postoperative management for both groups will include elevation of the foot for the initial 72 h after surgery and stitches removed in 10–14 days. Analgesics and antibiotics will be prescribed for the first 14 days after surgery, with weight bearing as tolerated.

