#### Strategies to improve adherence to interventions {11c}

Adherence to the randomised intervention allocation will be assessed by comparing the patient osteotomy group allocation as identified in the operation report, to the trial master sheet with the allocation information. Follow-up and PROM compliance will be encouraged through follow-up reminders, as part of the SOFARI registry processes. The primary outcome will be collected electronically, with controls in place to prevent partial completion of the questionnaire.

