#### Adverse event reporting and harms {22}

An adverse event is defined as any deviation from the normal recovery trajectory requiring alteration to the patient’s care or medical intervention. Adverse events will be collected after the subject has provided consent and enrolled in the trial. A serious adverse event (SAE) for this study is any untoward medical occurrence within the follow-up period of the study and results in any of the following: life-threatening condition, severe or permanent disability, prolonged hospitalisation or a significant hazard. Investigators will determine the relatedness of an event to the trial based on a temporal relationship to the intervention, as well as whether the event is unexpected or unexplained given the subject’s clinical course, previous medical conditions and concomitant medications. A separate form will be set up for adverse reporting, to be completed by the evaluator or the trial monitoring team based on updated clinical notes for the patient within the practice management system and electronically linked to the study database.

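### An allocation code cannot mask a fellow or assistant who watched the operation, so evaluations before 12 months by a fellow who assisted are unblinded although the protocol calls them masked

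*Protocol article*

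**What the plan says.** All of the blinding text is in the protocol article under Who will be blinded {17a}. Two roles are conceded to be unblinded: "Blinding is not feasible for the treating surgeon or the senior data engineer responsible for coding the randomisation sequence". Everyone else on the study side is declared blinded: "Surgical assistants, practice staff, clinical outcome assessors members of the research team and study statisticians involved in the data analysis will be blinded". Postoperative clinical evaluations and the assessment of serious adverse events are "conducted by a surgical fellow that is hosted within the clinic on a rotating basis for 6 months". The section foresees that this fellow may also have assisted at the operation, and its answer is that where the "surgical fellow assisting with surgery also performs the postoperative evaluation, masking will occur through access to only the allocation coding". A separate sentence reserves the 12-month evaluation for a fellow who took no part in the operation. No such rule is given for earlier evaluations.

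Intervention description {11a} sets out the two procedures. Group A has one saw cut, after which the head is moved proximally. Group B is prepared in the same way, but the operation is modified by "adding a second osteotomy proximally to remove a rectangular wedge of bone".

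Secondary outcome analysis counts complications that occur by the end of the 12 months. Methods for additional analyses {20b} adds, if more than 5% of participants overall have a complication, a Cox regression on time to detection that starts on day 1 after surgery.

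**The concern.** The protocol treats an assistant in theatre as blinded because that person sees only a neutral code. But the arms differ in what is done at the table, in plain view, so the assistant knows the technique whatever label is attached to the record.

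This matters where the same person later decides whether a complication is present and when it was first seen. Knowledge of the arm can make an evaluator look harder in one group, call a borderline finding differently, or date it earlier or later. Secondary outcome measures says that floating toe is rated by hand from a photograph and does not name the rater, so some judgement is involved. In the Cox analysis the date of detection is itself the outcome. Adverse events by treatment group can also prompt the investigators to review and stop the trial (Interim analyses {21b}), and no data monitoring committee is planned ({21a}).

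As written, the trial would also report blinding of assistants and of all outcome assessors, which its own surgical description rules out.

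**Working it through.** No arithmetic applies, because the plan gives no figure for the share of evaluations done by a fellow who assisted. The check sets the sections side by side.

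1. **Can the arms be told apart in theatre?** Yes. Intervention description {11a} gives one cut and a proximal shift for group A. For group B it gives a second cut and removal of a rectangular piece of bone. The difference is visible to anyone assisting.

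2. **Does the code hide this?** No. Under Sequence generation {16a} the code is a label from which study personnel other than the treating surgeon cannot infer the allocation. It controls what can be learned from the record. It does not act on what was seen at the operation. The reason that makes blinding infeasible for the surgeon applies equally to an assistant.

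3. **Does the protocol allow that person to evaluate outcomes?** Yes. {17a} provides for it explicitly and relies on coding alone.

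4. **When can it happen?** Before 12 months only, since the 12-month evaluation is assigned to an uninvolved fellow. If a fellow serves a single 6-month rotation (an assumption about how the rotation works), the fellow who assisted can evaluate that patient only within 6 months of surgery. The protocol places complications early too: {20c} describes them as acute when arguing that few will be missing.

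5. **Do those evaluations reach an analysis?** Yes, by two routes. The secondary outcome is cumulative to 12 months, so an early detection counts. The Cox analysis uses the detection date from day 1.

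6. **What is not reached?** FAOS-Pain is completed by the patients, and {17a} states that they are blinded. The assistant's knowledge does not enter that score directly.

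Steps 1 to 3 establish the contradiction. Steps 4 to 6 limit it to evaluations before 12 months by a fellow who assisted at that patient's operation, and to the complication and safety data.

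**The case against.** The strongest reply is that the exposure may be small. {17a} makes the overlap conditional, fellows rotate, and the 12-month visit is independent. A floating toe that is missed early but persists can still be recorded by the uninvolved fellow, so an early miss would mainly shift a date in the additional Cox analysis. Bias in incidence would need early over-calling, or transient events that are gone by 12 months. Floating toe also has a stated criterion (no floor contact when bearing weight) and a photographic record, and nothing says that the assisting fellow rates the photograph. Failure of union is judged by the 12-month review. All of this stands, and it limits the consequence. It does not repair the statement that a code masks someone who was at the operation.

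Several stronger readings are tempting, and the documents do not support them:

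- **That all complications found before 12 months are assessed unblinded.** This is certain only where the evaluator assisted at that patient's operation.
- **That a size of bias can be given.** One could assume that 10% to 20% of floating toes are missed in one arm, apply this to the 36% occurrence quoted in Secondary outcome measures (0.36 × 0.10 = 3.6 points; 0.36 × 0.20 = 7.2 points), and compare the result with the 15% reduction in Sample size {14}. The miss rate is invented, it is applied to a whole arm, and recapture at 12 months is ignored. The 15% reduction is planned from a 60% baseline for complication incidence, which is a different quantity from the floating-toe rate.
- **That the adverse-event form reveals the arm.** The form is "to be completed by the evaluator or the trial monitoring team based on updated clinical notes for the patient", and {18a} places surgical details in the practice system. But the "patient osteotomy group allocation as identified in the operation report" is mentioned in {11c} for an adherence check, and no section says that the evaluator reads the operation report.
- **That one witnessed case decodes the label for every patient.** This would follow if each arm had one fixed label, which the documents do not say.

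**Conclusion.** The point holds as a contradiction between {17a} and {11a}. Surgical assistants, and any fellow who assisted, are not blinded to the technique, and coding cannot make them so. Evaluations and serious adverse event assessments before 12 months by a fellow who assisted at that patient's surgery are unblinded, and they contribute to the secondary outcome and to the additional time-to-detection analysis.

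The extent is unknown and no bias can be quantified from the documents. The conclusion needs only one assumption, that a person assisting at a forefoot osteotomy can see whether a second cut is made and bone removed. It is a correction that should be made, but it does not threaten the primary comparison directly.

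**What to change.** 1. In {17a}, move surgical assistants and any fellow who assisted to the list of those not blinded, and delete the claim that coding masks them.

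2. Keep the secondary outcome as cumulative incidence to 12 months. Counting only what is present at the 12-month visit or visible on images would drop complications that had resolved or been reoperated. It would also conflict with the time-to-detection analysis.

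3. Have the coded floating-toe photographs and the radiographs, including earlier ones, rated by the uninvolved fellow already planned for 12 months, without access to the operation report. For radiographs this relies on the protocol's own expectation that the technique cannot be read from them.

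4. Some early complications will be recorded only by a fellow who assisted. An example is stiffness, for which the article names no image that could be re-rated. Flag these as unblinded assessments, repeat the secondary analysis with blinded-rated events only as a sensitivity analysis, and report the limitation. The restricted analysis can lose transient events, so it should stand beside the main analysis and not replace it.

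The cost is a little extra rating and analysis work with staff and images already planned, and a less favourable blinding statement. The randomisation, the sample size and the primary analysis do not change.

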## Introduction

### Background and rationale {6a}

Propulsive metatarsalgia is defined as pain under one or more metatarsal heads during the “third rocker” phase (30 to 60%) of the gait cycle, from heel lift-off to the end of propulsion by the great toe [1]. Weil osteotomy is a reliable distal oblique osteotomy procedure performed to treat lesser metatarsal deformities and alleviate metatarsalgia, by shortening the metatarsal in the transverse plane. The osteotomy is performed with or without adjunct procedures for toe correction, which may include proximal interphalangeal arthrodesis [2], fusion/arthrodesis of the first metatarsophalangeal (MTP) joint [3] or hallux valgus correction [4]. While Weil osteotomies are commonly performed, complications include floating toe, joint stiffness, avascular necrosis, transfer of metatarsalgia to subsequent toes and plantar flexion of the metatarsal [1, 5, 6].

Traditional flat-cut Weil osteotomies involve a single distal oblique incision in the dorsal aspect of the metatarsal head, with translation of the head by 5–10 mm. Wedge-cut osteotomy is a modification of the flat-cut Weil procedure and includes a second incision to remove a slice of bone [1]. A wedge is created either with parallel sides or with an apex on the plantar aspect of the metatarsal, and the procedure is purported to reduce plantar translation of the metatarsal head, maintain the MTP centre of rotation and improve intrinsic muscle function as demonstrated on sawbone models [7]. However, there is limited in vivo data for the clinical efficacy of this technique, and the quality of evidence is lacking [7, 8].

The proposed study has therefore been designed to investigate whether the modified wedge-cut Weil osteotomy compared to the flat-cut technique, with or without required adjunct procedures, is associated with increased pain relief and fewer complications at up to 12 months postoperatively in patients presenting with propulsive metatarsalgia.

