### Data collection and management

#### Plans for assessment and collection of outcomes {18a}

Patient personal and medical data is routinely collected and stored in the participating surgeons’ practice management systems (Bluechip, MedicalDirector, Australia and Genie, Genie Solutions, Australia). Patient demographic data, comorbidities and full patient history relating to the history and onset of the foot and ankle condition will be recorded in the practice management system during patient consultation. Radiological reports collected routinely as part of diagnosis, surgical planning and postoperative follow-up, full description of diagnosis, mode of treatment and details of nonoperative and surgical interventions, and timing of treatments will also be recorded in the practice management system during patient consultation. Intraoperative data, patient-reported outcomes data and findings from clinical examination will be electronically entered into the SOFARI registry via web-based forms (Google Suite, Google, USA) by the clinical research nurse, research team, surgeon or the patient.

Intraoperative (surgical technique), patient-reported (FAOS-Pain) and clinical outcome (complications) data collected during this trial will additionally be linked to the SOFARI registry via the same modes of data entry. Data collection will continue until the minimum sample size requirements for the study are met with complete records established.

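### The blinding section limits assessors, practice staff and the research team to an allocation code, but other sections give these roles notes and data that record the surgical technique

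*Protocol article*

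**What the plan says.** Section {17a} names the treating surgeon and the senior data engineer as unblinded. Surgical assistants, practice staff, outcome assessors, the research team and the statisticians are declared blinded, "with access to only the allocation code which will comprise a label where grouping is not able to be inferred". The Principles paragraph under {20a} adds: "An analyst blinded to treatment allocation will perform the primary and secondary analyses".

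On assessment, {17a} states: "Postoperative clinical evaluations and assessment of serious adverse events will be conducted by a surgical fellow". The fellow may have assisted at the operation, in which case masking rests on the code alone. At 12 months the assessor is a fellow who took no part in the surgery. The evaluator may see postoperative radiographs, and "it is expected the intervention allocation cannot be derived from these images".

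Other sections describe where these people get their information:

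- {22}, on the adverse-event form: "to be completed by the evaluator or the trial monitoring team based on updated clinical notes for the patient within the practice management system".
- {18a}, on what that system holds: "details of nonoperative and surgical interventions, and timing of treatments will also be recorded in the practice management system".
- {18a}, on the registry: "Intraoperative (surgical technique), patient-reported (FAOS-Pain) and clinical outcome (complications) data collected during this trial will additionally be linked to the SOFARI registry". The research team is among those listed as entering intraoperative, patient-reported and examination data.
- {11c}: adherence is checked by comparing the osteotomy group shown in the operation report with the master sheet.
- {19}: the registry is the trial's primary data source, intraoperative data included, and the research team enters the practice software for audits.
- {23}: audits compare the masterlist with the practice system in 10% of patients.

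**The concern.** A neutral label blinds someone only if the label is all that person sees. Here the same people are sent to records that describe the operation. If the label is shared by all patients in an arm (the article does not say), one patient whose technique is known decodes it for everyone.

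The outcomes exposed are those that depend on a rater's judgement. Floating toe is rated by hand from a photograph. Stiffness is named as a procedure-specific complication in the Objectives. Union is graded by cortical continuity at the osteotomy. Adverse-event judgements matter too, because under {21b} a high incidence in either group may lead the investigators to end the trial. The working hypothesis favours the wedge-cut, and the secondary sample size uses a one-sided test, so rating bias in the expected direction would count towards a positive result. The trial could also report a degree of blinding that it did not have.

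**Working it through.** No formula applies: the protocol states no figure on this point. The check sets the blinding statement beside the data flow, role by role.

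1. **Evaluator completing the adverse-event form.** {17a} allows only the code. {22} has the evaluator or the monitoring team work from practice-system notes, and {18a} places surgical details in that system. The two statements conflict for this role.

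2. **Research team.** {17a} allows only the code. {18a} lists the team among those who may enter intraoperative data, and surgical technique reaches the registry by the same forms. {19} sends the team into the practice software. {23} adds spot checks in 10% of patients; on the planned 80 that is 0.10 × 80 = 8 patients. These statements also conflict.

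3. **Adherence check.** {11c} needs someone to read the operation report, which identifies the group, against the master sheet. {17a} ends the engineer's involvement at allocation and data coding, so the check has no clearly unblinded owner.

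4. **Fellow who assisted at surgery.** Someone present at the operation can see which technique is used, so a coded label cannot mask it afterwards. This affects evaluations before 12 months. The rule of a different fellow at 12 months removes that exposure for the final visit, but not exposure through notes or images.

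5. **Radiographs.** {11a} gives the arms different bone cuts. {6a} says of the wedge-cut that "the procedure is purported to reduce plantar translation of the metatarsal head, maintain the MTP centre of rotation". No section says whether the difference can be seen on a film. The sentence in {17a} is an expectation, and no check of it is stated.

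6. **Statisticians.** The registry holds the technique field and supplies the trial. The article states no step that removes the field from the analysis file. The engineer's data coding may do so.

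7. **Primary outcome.** FAOS Pain is completed electronically by participants declared blinded. None of the routes above gives them the technique.

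**Why no size in percentage points is given.** Suppose the true complication rate is p in both arms, and a share m of control non-events is rated up and of wedge-cut events rated down. The false gap is m(1 − p) + mp = m, whatever p is. With m = 10% it is 10 points at p = 45% (50.5% against 40.5%) and at p = 60% (64% against 54%). The calculation only returns the assumed m, and the documents supply no value for m.

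**The case against.** The strongest reply is that much of this is inference.

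- **Radiographs.** A reader might infer that the films reveal the technique. The documents do not support that. Reduced plantar translation is described as purported, from sawbone models with limited in vivo data. Group B is a modification of group A, and the overhanging ledge in group A is resected. Whether a reader could tell the arms apart needs imaging evidence that is not here. This objection stands: the expectation is untested, not shown to be false.
- **Analysts.** A reader might infer that the statisticians see the technique field. No section says so. Data coding belongs to the engineer, and extract rules are commonly left to a full protocol or analysis plan. This stands too, so the analyst point is a request for one clarifying sentence.
- **Surgeon entry.** The list in {18a} pools three data types and four kinds of person, including the patient. It does not establish that the surgeon enters complication ratings, and {17a} gives postoperative evaluation to the fellow.
- **12-month visit.** Floating toe is rated from a photograph, and no section says that radiographs or operation reports are read first. Equally, no section sets the order.

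What the objection does not remove is the conflict for the adverse-event form and the research team. There the document itself names the records used and says what they contain.

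**Conclusion.** The point holds as an internal contradiction. {17a} cannot limit assessors, practice staff and the research team to the code while {11c}, {18a}, {19}, {22} and {23} give these roles sources that carry the technique. It is worth correcting, but it does not undermine the trial's main comparison. The risk lies with the secondary complication outcome (hand-rated floating toe, stiffness, union) and with adverse-event judgements. It cannot be sized from the documents.

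Two assumptions matter. First, the notes used for the adverse-event form are taken to include, or sit beside, the surgical details stored in the same system. Second, the list of blinded roles in {17a} is taken to cover the research team as a whole. Its punctuation would also allow only those members involved in the data analysis, which would weaken the research-team part but leave the evaluator and the assisting fellow as they are.

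**What to change.** 1. Reconcile {17a} with {11c}, {18a}, {19}, {22} and {23}, stating for each role which records it may open.
2. Have the evaluator rate and lock floating toe (from the photograph) and stiffness before opening radiographs or notes.
3. For trial purposes, restrict the technique field and the operation reports to the senior data engineer until database lock. Amend the limit on the engineer's role in {17a} so that this person can do the adherence check.
4. State that the treating surgeon does not enter complication ratings.
5. Reword the radiograph sentence as an untested assumption. Describe union grading, and evaluations by a fellow who assisted at the surgery, as not reliably blinded.

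The cost is wording, the order of forms and access permissions in the existing registry, without added staff. The engineer takes on slightly more work, and the trial must describe its blinding less favourably.
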